### Outcome measures

The primary outcome measure is the incidence of superficial or deep incisional SSI within 30 days of surgery involving any of the operative incisions made. This measure adopts the definitions within the 2008 Centre for Disease Control and Prevention^21^ definitions of SSI (box 2). Where it is unfeasible to follow-up the patients after discharge for 30 days postoperatively, in-hospital SSI incidence will be used as a proxy measure.Box 2Centre for Disease Control and Prevention (CDC) criteria for surgical site infection (SSI)^21^
CDC criteria for SSI require the patient to have at least one of the following:Purulent drainage from the superficial or deep (fascia or muscle) incision but not from within the organ/space component of the surgical siteAt least one of the following: pain or tenderness; localised swelling; redness; heat; fever and the incision is opened deliberately or spontaneously dehiscesAbscess within the wound (clinical, histopathological or radiological detection)

The secondary outcomes that will be derived from this study include:a description of the global variation in organisms causing SSI (including use of microbiological tests);the incidence of antibiotic-resistant pathogens detected in patients with SSI;30-day POMR;30-day postoperative reintervention rate;assessing how difference in SSI rates varies based on the method by which patients are followed up.

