**Surgical site infection**	
Prior to discharge	Yes, No
At 30 days after surgery	Yes, No, Not assessed after discharge
	*If yes:* Was a wound swab sent for microbiological culture: Yes, No—but available in this centre, No—not available in this centre
	*If yes:* How was this treated: operative drainage, wound opened outside of operating theatre, antibiotics (tick all that apply)
What bacteria, if any, were identified?	None, *Staphylococcus aureus*, Coliform, Anaerobe, Other (five tick boxes)
	*If yes*: Sensitivity: sensitive to antibiotic prophylaxis given; resistant to antibiotic prophylaxis given; sensitivities not tested—but available in this centre; sensitivities not tested—not available in this centre
30-day unexpected reintervention. Record the most serious reintervention	Yes—surgical, Yes—endoscopic, Yes—interventional radiology, No
30-day mortality	Dead, Alive, Unknown. *If died:* postoperative day of death
30-day intra-abdominal/pelvic abscess (CT, ultrasound or clinical (including reoperation) evidence of intra-abdominal or pelvic abscess)	Yes, No
Other hospital-acquired infection (treated with or without antibiotics)	Yes—urinary tract infection, Yes—pneumonia, Yes—central venous line infection, Yes—peripheral line infection, Yes—other, No
How was 30-day follow-up status achieved? (all applicable)	Still an inpatient, Clinic review, Telephone review, Community/home review, Discharged before 30 days and not contacted again

ASA, American Society of Anaesthesiologists; GI, gastrointestinal; NSAID, non-steroidal anti-inflammatory drug; PCV, packed cell volume.

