### Investigators

The study will be undertaken by investigators around the world who will be responsible for disseminating the protocol at their individual site, ensuring appropriate study approvals are in place and collecting and uploading data to an online REDCap database. A central study writing committee compromising of an internationally representative group of healthcare professionals will be responsible for data analysis, final manuscript drafting and submission. Individuals will be required to register their unit via the REDCap system and will be required to complete two training modules prior to starting.

Countries with multiple sites will be assigned a country lead, who will be responsible for coordinating multiple teams across sites to ensure duplication of data does not occur. Each hospital will have a primary local investigator who will act as guarantor of data. A maximum of three local investigators can cover each 2-week data collection period. They will be responsible for gaining local audit, service evaluation or research ethics approval as appropriate to their institution. Investigators should also create clear mechanisms to identify and include all eligible patients, which involves daily review of operating logbooks, emergency admission lists and team handover lists. They should identify clear pathways to accurately collect baseline and follow-up data and be proactive in identifying postoperative events within the normal limits of follow-up.

Local arrangements for follow-up may include daily review of the patient and notes during admission and before discharge in order to identify in-hospital SSIs, reviewing patient status in outpatient clinics or via telephone interview at 30 days (if this normal practice), checking hospital notes (paper or electronic) and looking at handover lists. All investigators will be listed as collaborators on resulting publications.

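### The 30-day reintervention and abscess fields cannot record unknown status, and the follow-up list has no notes-review code, so the reintervention rate may be understated

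*Protocol article*

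**What the plan says.** Table 1 (Data points) is the list of required fields with their response options. Its last block holds four 30-day items:

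- SSI at 30 days: "Yes, No, Not assessed after discharge".
- Mortality: "Dead, Alive, Unknown".
- Unexpected reintervention: "Yes—surgical, Yes—endoscopic, Yes—interventional radiology, No".
- Intra-abdominal or pelvic abscess ("30-day intra-abdominal/pelvic abscess (CT, ultrasound or clinical (including reoperation) evidence of intra-abdominal or pelvic abscess"): yes or no.

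The same block asks how follow-up was achieved, with all applicable options ticked. The options are still an inpatient, clinic, telephone, community or home review, and "Discharged before 30 days and not contacted again".

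Outcome measures names the "30-day postoperative reintervention rate" as a secondary outcome, and also the comparison of SSI rates by method of follow-up. Abscess is not on that list. The section foresees centres that cannot follow patients after discharge and gives an in-hospital substitute, for SSI only. Investigators makes telephone review conditional on normal practice and allows status to be found by "checking hospital notes (paper or electronic) and looking at handover lists". Study setting excludes centres with more than 5% missing data, counted over all data points, and removes them from authorship.

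**The concern.** The form recognises that 30-day status can be unknown for SSI and mortality, but gives no way to say so for reintervention and abscess. For a patient who went home and was not contacted, the investigator can only enter *No* or leave the field empty, and the missing-data rule discourages empty fields. If *No* is entered, the patient counts as event-free in a rate labelled 30-day, when all that is known is that nothing happened before discharge. The reported figure then mixes 30-day and in-hospital rates, and can only err downwards.

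The second gap concerns the follow-up variable itself. A discharged patient whose status came only from the notes has no code of their own. The nearest true option is the not-contacted code, which also covers patients about whom nobody looked further. That variable defines the groups in the planned analysis of SSI by follow-up method.

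**Working it through.** The article gives no reintervention rate, no share of events after discharge and no expected follow-up rate, so there is no stated figure to reproduce on this point. Its sample-size figure concerns SSI and is not an input.

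**Step 1. Codes side by side.**

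| 30-day item | Code for unknown status | Role in Outcome measures |
|---|---|---|
| SSI | yes | primary |
| Mortality | yes | secondary |
| Reintervention | none | secondary |
| Abscess | none | not listed |

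**Step 2. Effect of entering *No*.** Let p be the true 30-day reintervention rate, L the share of patients not contacted after discharge and entered as *No* unless an event is known, and q the share of events that arise after discharge and stay unknown to the centre in such patients. Take events to be equally frequent in contacted and uncontacted patients.

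Recorded rate = p(1 − L) + pL(1 − q) = p(1 − qL).

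The relative understatement is q × L, whatever p is.

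**Step 3. Numbers (all inputs assumed).** Relative understatement:

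| q | L = 0.05 | L = 0.1 | L = 0.2 | L = 0.4 | L = 0.6 |
|---|---|---|---|---|---|
| 0.2 | 1% | 2% | 4% | 8% | 12% |
| 0.4 | 2% | 4% | 8% | 16% | 24% |
| 0.6 | 3% | 6% | 12% | 24% | 36% |

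With p = 5%, for example, the recorded rate is 4.95% at q = 0.2, L = 0.05; 4.6% at q = 0.4, L = 0.2; and 3.2% at q = 0.6, L = 0.6.

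**Step 4. How hard the missing-data rule pushes.** Table 1 has about 35 fields that apply to every patient (own count, conditional sub-items left out). Leaving both fields blank for every patient gives 2/35 = 5.7% missing; for half the patients, 2.9%. Alone, the two fields pass 5% only when the uncontacted share exceeds 0.05 × 35/2 = 87.5%. They add to other missing items but would seldom exclude a centre by themselves.

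**Step 5. What a recode does.** Suppose *No* is set to unknown for patients whose only follow-up code is the not-contacted one, while their recorded *Yes* answers stay. The rate becomes p(1 − qL) / [(1 − L) + Lp(1 − q)]. With p = 5%, q = 0.4, L = 0.4 this is 0.042 / (0.60 + 0.012) = 6.9%, against 4.2% as recorded and 5% in truth. The recode can therefore overshoot, because it keeps events and drops non-events in the same group. One rate alone is not enough.

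**The case against.** The strongest reply is that the data to repair this are already collected. The not-contacted code sits in the same record, as do the not-assessed code for SSI and the unknown code for mortality, so an analyst can choose a denominator from them. A reader might infer that unknown patients cannot be separated at all; the documents do not support that. What stands against the reply is narrower. The not-contacted code does not say whether the notes were checked, so a real *No* and an unexamined one look alike. The neighbouring codes give hints, but the form does not define them for this use.

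Other stronger readings also fail:

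- **Lost patients are coded *No*, so the outcome is biased.** Nothing in the article instructs this. It is an inference from the options offered and the discouragement of blanks, and that discouragement is modest (Step 4).
- **Several secondary outcomes are affected through these two fields.** Abscess is collected but not a listed outcome, so the fields touch one secondary outcome, reintervention.
- **Notes-only patients are miscoded.** A discharged patient known only from notes was indeed not contacted, and notes of a clinic visit can be ticked as clinic review. The fault is lost distinction.
- **Comparisons between development settings are distorted.** With p = 5% in both settings and L of 10% against 50%, the apparent odds ratio would be 0.91, 0.83 or 0.74 at q = 0.2, 0.4 or 0.6. But these inputs are assumed, the adjusted model by Human Development Index is described for SSI, and the article calls such comparisons hypothesis generating.
- **An SSI that healed before day 30 is lost because the item asks about status at 30 days.** The outcome is defined as SSI "within 30 days of surgery involving any of the operative incisions made", a pre-discharge item sits beside it, and investigators are trained on the definition. This is mainly a matter of label wording.

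It is also fair that reintervention is a hospital event. A readmission to the same hospital can be found in its notes, which lowers q. Detailed denominators may stand in the full protocol; the response options, however, are fixed in this article.

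**Conclusion.** The point holds as a gap in the form. Reintervention and abscess lack the unknown code that SSI and mortality have, and the follow-up list omits a route that the article permits. If uncontacted patients are entered as *No*, the direction of error in the 30-day reintervention rate is certain: downwards, by q × L in relative terms. The size cannot be fixed from the documents; 1% to 36% is a range over assumed inputs, and it rests on equal event rates in contacted and uncontacted patients. The analysis of SSI by follow-up method loses the distinction between notes checked and never checked. The primary outcome keeps its own not-assessed code and its in-hospital substitute, so this part of the form does not affect it.

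**What to change.** Add a not-assessed-after-discharge option, as SSI already has, to the reintervention and abscess fields. Add 'Hospital notes review only' to the follow-up list. A separate code for death before day 30 is not needed, since the mortality field records death and its day. Report 30-day reintervention among patients with known 30-day status, and define known status by how follow-up was done and not by the answer given, so that events and non-events are kept or dropped alike.

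If the database is closed, treat *No* as unknown when the only follow-up code is the not-contacted one, and show the rate both ways, as recorded and after the recode. Step 5 shows why neither should stand alone. A third rate that leaves these patients out of numerator and denominator is a useful addition.

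The cost is a few options in REDCap, or one recode rule and an extra line in a table. The downside is a smaller denominator, and after a recode some patients with a valid *No* from notes are set aside with the rest.

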### Investigators

The study will be undertaken by investigators around the world who will be responsible for disseminating the protocol at their individual site, ensuring appropriate study approvals are in place and collecting and uploading data to an online REDCap database. A central study writing committee compromising of an internationally representative group of healthcare professionals will be responsible for data analysis, final manuscript drafting and submission. Individuals will be required to register their unit via the REDCap system and will be required to complete two training modules prior to starting.

Countries with multiple sites will be assigned a country lead, who will be responsible for coordinating multiple teams across sites to ensure duplication of data does not occur. Each hospital will have a primary local investigator who will act as guarantor of data. A maximum of three local investigators can cover each 2-week data collection period. They will be responsible for gaining local audit, service evaluation or research ethics approval as appropriate to their institution. Investigators should also create clear mechanisms to identify and include all eligible patients, which involves daily review of operating logbooks, emergency admission lists and team handover lists. They should identify clear pathways to accurately collect baseline and follow-up data and be proactive in identifying postoperative events within the normal limits of follow-up.

Local arrangements for follow-up may include daily review of the patient and notes during admission and before discharge in order to identify in-hospital SSIs, reviewing patient status in outpatient clinics or via telephone interview at 30 days (if this normal practice), checking hospital notes (paper or electronic) and looking at handover lists. All investigators will be listed as collaborators on resulting publications.

### Quality of data

To ensure high data quality, a detailed protocol has been produced and published online. The protocol has been translated into common languages to ease investigator understanding, including Chinese (traditional and simplified), Spanish, Italian, Greek, Portuguese and Arabic.^23^ In addition, investigators are mandated to complete two online educational modules, one a summary of the study protocol and the other an overview of the diagnosis and classification of SSI.

### Data validation

Data validation will be performed in two parts across a group of representative centres. Case completeness assessment will involve an independent investigator ascertaining the number of eligible cases within a 2-week data collection period at a participating centre and comparing this to actual number of cases submitted. Data accuracy will be assessed using qualitative, semistructured interviews with investigators to assess local data collection methods.

### Statistical analysis and power calculation

Identification of hospital or surgeon-specific performance will not be reported. Variation in outcome across different contexts will be tested using the HDI^24^ (a composite statistic of life expectancy, education and income indices). Following analysis, centre-specific SSI rates will be fed back to participants. Hierarchical logistic regression multivariate analysis will be used to adjust the influence of HDI on SSI rates for confounding patient and disease variables. We will subgroup patients according to operative procedure for the purpose of analysis.

An appropriate sample size is difficult to calculate in this setting as there is a lack of previous study data to indicate the incidence of SSIs internationally. The previous GlobalSurg study recruited 10 745 patients using the same methodology.^25^Although the inclusion criterion for this study is different, we expect to achieve a similar number of patients. Based on the findings from GlobalSurg 1, this number will provide adequate power to show a minimum difference from 7% to 10% in SSI rate between two groups (80% power at 5% alpha requires a sample size of 1350 patients).

### Trial registration number

This study has been registered with ClinicalTrials.gov (identifier: NCT02662231). The registration is available to view via: https://clinicaltrials.gov/ct2/show/NCT02662231.

### Ethics and dissemination

#### Research ethics approval

The primary audit standard stems from the UK National Institute for Health and Clinical Excellence guidelines^26^ (box 3). As this study will not change local clinical practice and is limited to using data obtained as part of usual care, it has been classified as an audit by the South East Scotland Research Ethics Service in Edinburgh, Scotland (online supplementary file 1). Thus, this may be considered a global audit or global service evaluation.Box 3Study audit standards^27^
Audit standards from National Institute for Health and Clinical Excellence: SurveillancePeople having surgery are cared for by healthcare providers that monitor surgical site infection rates (including postdischarge infections) and provide feedback to relevant staff and stakeholders for continuous improvement through adjustment of clinical practice (Quality Statement 7).Treatment of surgical site infection:People with a surgical site infection are offered treatment with an antibiotic that covers the likely causative organisms and is selected based on local resistance patterns and the results of microbiological tests (Quality Statement 6).

10.1136/bmjopen-2016-012150.supp1Supplementary file 1

Investigators are required to gain approval from the relevant responsible bodies, including local clinical audit departments, research and development departments or institutional review boards, as appropriate in their centre. If such departments are unavailable, written permission should be supplied by the chief of surgery or the responsible supervising consultant/attending physician.

#### Protocol dissemination

The protocol will be disseminated across the established GlobalSurg network, compromised of surgeons, medical students and research nurses across the world. The network previously included over 1200 collaborators across 375 centres representing 58 countries.^12^ Country leads are responsible for local coordination and dissemination within their country. In addition, the use of social media including Facebook, Twitter and YouTube has been shown to be an effective medium for dissemination of such collaborative projects^27^ and will also be employed.

#### Dissemination of results

We aim to publish the study results as open access. Data from the study will be described to ensure individual countries, hospitals and surgeons are anonymous and then shall be deposited in an online data repository for others to analyse. Based on the results of GlobalSurg 2 Study, a quality improvement protocol and/or interventional clinical trials will be suggested for possible application in the infection control units of each hospital included in this study.

## Discussion

In this study protocol, we describe a multicentre, international, prospective cohort study investigating the incidence of SSI and its association with preoperative parameters and risk factors as well as with postoperative morbidity and mortality. Despite SSI being the most common complication following major gastrointestinal surgery, no data exist describing its global epidemiology. Similarly, appendicectomies and cholecystectomies are two of the most common intra-abdominal operations performed; yet the international burden of SSI for these patients remains unknown.

By using collaborative methodology^17^ and a short 2-week data collection period, the study will recruit sufficient numbers of patients to inform this, while avoiding burdening low-resource centres that may otherwise be unable to participate. By investigating the morbidity and mortality caused by SSIs globally, this study will provide a platform to build future quality improvement programmes and interventional trials.

This study will be delivered using an international multidisciplinary collaborative network of healthcare researchers. The collaborative model has consistently proven potential for producing high-quality outcomes data with limited resource requirements across national^6 18 28^ and international studies.^4^ A detailed study protocol and mandatory completion of online training modules will ensure standardised definitions and understanding of SSI so that this study will deliver a reliable and accurate data set. A predefined data validation strategy will produce an estimate of case ascertainment and the quality of local methods used to gather data.

SSIs have been shown to increase costs by an average of US$20 842 in high-income countries, which significantly burden healthcare systems.^29^ Within low-income countries, healthcare-associated infections have been estimated to have an increased incidence.^30^ This can result in an increased length of stay of an average 9.7 days longer and has further knock-on effects to dependants which are more profound in the low-income setting.^29^ To help address this fiscal disparity, this project will inform future service-level quality improvement programmes. When regular audits of pathogens and antibiotic prescribing are undertaken, redundant antibiotic use is reduced.^31 32^ With feedback of baseline SSI rates to participating centres, collaborators have the opportunity to appraise their current practice against a global standard. Surgeons will be able to implement interventions to improve service provision prior to a reaudit, 1 year in the future. With the savings made from the implementation of prevention programmes being 11 times greater on average than costs,^33^ these programmes will help reduce fiscal burden to patients and public health systems.

Many important determinants of a high burden of SSI in developing countries have not been identified.^5^ This study will be able to identify an association between SSIs and various risk factors, however, due to its observational nature, it will not be able to prove causality. Therefore, data points collected have been included with a plausible relationship with SSIs. The number of data collection points has been kept short in order to maximise data completeness and accuracy and minimise investigator workload.

Finally, this study will continue to strengthen the GlobalSurg network, developing capacity for research in LMICs.^34^ For the many research-naive centres worldwide, participation in this project could instil a culture of clinical effectiveness into routine clinical practice. This study will ultimately provide the basis for a global multicentre randomised controlled trial, aimed at reducing the burden of SSI and its attributed morbidity and mortality.
